Each participant is assigned to a personal lay counselor (supervised by a clinical psychologist) to support the participant in following the online program. Over the course of the program, the lay counselors provide brief feedback online regarding the assignments for each of the eight modules via the online program. In addition, the lay counselors will make brief contact via phone calls to reinforce and encourage participants to work in the online program (weekly during the first 4 weeks and at weeks 6 and 8) in order to enhance adherence to the program and to prevent attrition. The calls do not take more than 20 min each and there is no option for a face-to-face contact.

The GAF-ID program is equipped with a messaging facility that will be used as the main medium of communication between the participants and their lay counselors. The lay counselors log into the GAF-ID program regularly to see the assignments that have been undertaken by the participants and to provide feedback consistent with the BA rationale. If a module has been completed satisfactorily, the lay counselor sends a short message through the GAF-ID program with feedback on the previous module and encourages the participants to engage in the next module. If the participants cannot finish the assignments or seem to not understand the instructions, they can send a message to their lay counselors, and the lay counselors will provide assistance. Further, the lay counselors can see the log-in history of the participants they have assisted, and can send reminders via email and text message to those participants who do not log in to the program each week. Phone calls will follow if the participant fails to reinitiate the intervention after one more week.

All lay counselors will work under the supervision of licensed clinical psychologists and regularly report on the participant’s progress to them as their supervisors. The lay counselors present their cases to their supervisors and address concerns in regular weekly supervision.

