#### Control condition: online-delivered minimal psychoeducation (PE)

In the PE group, as an active comparison condition, the minimal PE is presented as a short, online leaflet consisting of basic information about depression and basic tips on how it can be addressed, representing information that can be easily and freely accessed online outside of this program. Participants in the PE group will receive neither assistance from lay counselors nor from clinical psychologists, but provided with the same assessments as the intervention group.

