### Support

#### Lay counselors

We plan to recruit 20–30 persons to serve as lay counselors for this study. Our lay counselors meet the following criteria: (1) age between 20 and 40 years with no restriction on gender, (2) minimum senior high school education, (3) willing to participate fully during the trial process, (4) no professional background as a mental health specialist, and (5) willing to participate in the training for lay counselor in this study.

The focus of the lay counselors’ support is to help each participant follow the GAF-ID program by (1) explaining to the participants how GAF-ID works, (2) providing technical assistance for participants, (3) providing short feedback to each of the completed modules, and (4) reminding participants to complete each online module. The lay counselors will not provide any additional counseling.

All lay counselors receive 2 days of intensive training during which all features of the Internet-based BA are discussed and role-plays are conducted. Other technical issues addressed during the training include how to handle technical problems that may arise, how to handle participants with low motivation, and how to monitor suicidality or other serious deteriorations during the intervention. They will receive printed training modules to help them do their tasks during the trial.

To promote treatment integrity and consistency, we provided, apart from the 2 days of training, a treatment guidance protocol, a weekly structured support checklist, a participant’s short progress report template, and regular supervision by a clinical psychologist. In order to elicit and to monitor adherence, the lay counselors will fill out a weekly structured checklist on the support that they have given to each participant. To assure integrity and consistency further, the lay counselors will also be asked to write a regular short progress report on each participant. They will give both the checklist and the report to the clinical psychologists who supervised them. The clinical psychologists will then provide necessary feedback and consultations.

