#### Clinical psychologists

We plan to recruit 10–15 clinical psychologists to provide clinical supervision to the lay counselors in this trial. Each clinical psychologist will supervise three to five lay counselors. All clinical psychologists will be graduates from a formal clinical psychology program and need to be licensed as clinical psychologists in Indonesia. The clinical psychologists will receive a weekly structured support checklist and a short report of participants’ progress from the lay counselors under their supervision that they can discuss together in the regular supervision meetings.

Similar to what is provided for the lay counselors, the clinical psychologists will be provided with 2 days of intensive training on the GAF-ID program and a printed version of the training module. The training is given to make sure that the clinical psychologists are familiar with the program and can provide necessary supervision to the lay counselors.

The clinical psychologists will only have contact with participants in case of a suicidal crisis and other serious deteriorations, through phone calls. They will be equipped with the standardized procedure on when and how they should do suicide risk assessment and handle serious participant deteriorations within this trial.

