### Outcome assessments

There will be several points of assessment conducted during this study: baseline, post intervention (10 weeks from baseline), and follow-ups (3 months and 6 months from baseline). There will also be a biweekly (once every 2 weeks) assessment in between. All self-report assessments will be conducted through the Qualtrics website, with a private link delivered to the participant’s personal email at each time point. See Table 1 for the details.

**Table 1 Tab1:** Assessments

Measures	Description	Baseline (t0)	2 weeks	4 weeks	6 weeks	8 weeks	10 weeks (post intervention)	3 months (follow-up)	6 months (follow-up)
Primary measure									
PHQ-9	Depression symptoms level	+	+	+	+	+	+	+	+
Secondary measures									
SCID-5 (interview)	Current depressive disorder (major depressive disorder and persistent depressive disorder)	+					+		
IDS-SR	Depression symptoms	+					+	+	+
FQ	Fear and avoidance	+					+	+	+
MSPSS	Perceived social support	+					+	+	+
WHOQOL-BREF	Quality of life	+					+	+	+
Potential mediators and moderators									
VAS	General mood condition	+	+	+	+	+	+	+	+
PANAS	Positive and negative affects	+	+	+	+	+	+	+	+
BADS-SF	Behavioral activation	+	+	+	+	+	+	+	+
Life-events	Life events	+							
SCID-5 (interview)	• History of depressive disorders (major depressive disorder or persistent depressive disorder) • Trauma- and stressor-related disorders	+							
Childhood trauma (interview)	History of childhood trauma	+							
Additional measures									
MEIM	Multigroup ethnic identity measure	+							
Demographics	Sociodemographic characteristics	+							
Clinical information	Information related to clinical conditions	+							

*BADS*-*SF* Behavioral Activation for Depression Scale Short Form, *FQ* Fear Questionnaire, *IDS*-*SR* Inventory of Depressive Symptomatology Self-Report, *MEIM* Multigroup Ethnic Identity Measure, *MSPSS* Multidimensional Scale of Perceived Social Support, *PANAS* Positive and Negative Affect Scale, *PHQ*-*9* Patient Health Questionnaire-9, *SCID*-*5* Structured Clinical Interview for DSM-5, *VAS* Visual Analogue Scale, *WHOQOL*-*BREF* The brief version of the WHO Quality Of Life

The time frames of 2 weeks, 4 weeks, 6 weeks, 8 weeks, 10 weeks, 3 months, and 6 months are counted from baseline (applied in both groups)

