### Suicidality and serious deterioration

Suicidal thoughts and tendencies will be assessed biweekly in both conditions using the PHQ-9 [30] during the study. Participants scoring at least 2 on the suicide item “Thoughts that you would be better off dead or of hurting yourself in some way” twice in a row will be contacted by a clinical psychologist via a phone call for suicide risk assessment. Moreover, serious deterioration will be detected via the biweekly measures: in case an increase in depression level measured by the PHQ-9 [30] occurs (score increase by at least 5 points with a total score of at least 15 points) and this increase is still present or even more pronounced 2 weeks later, participants will be contacted by a trained research assistant for an IDS-C interview [34] via a phone call. If the score is at least 24, then a SCID-5 interview [31] on depression and screening for other potential deteriorations will follow. A full SCID-5 interview [31] for specific section will be followed if the participants answer “yes” to either of the screening questions.

For both treatment conditions, in case of severe suicidality and serious deterioration, more intensive treatment may be required and the participant may need to be referred to a mental health professional. They will be provided with appropriate referral information when necessary. However, all participants will be asked to continue with the intervention and the assessments.

At post intervention (10 weeks from baseline), as an outcome assessment, we will conduct the SCID-5 interview [31] on depression. At this point, we will also use the SCID-5 [31] to screen for other deteriorations in all participants, followed by the full section interview if the participants answer “yes” to either of the screening questions. The same referral procedure will be applied if any serious deterioration is found.

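### Both safety triggers need a second positive PHQ-9, so a participant (mainly in the psychoeducation arm) who falls silent after a first positive at week 2, 4 or 6 has no stated contact before week 10

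*Protocol article*

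**What the plan says.** The section on suicidality and serious deterioration gives two contact triggers, both applied to the 2-weekly PHQ-9 in both arms.

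- **Suicide item.** Participants with a score of at least 2 "twice in a row will be contacted by a clinical psychologist via a phone call for suicide risk assessment".
- **Deterioration.** A rise of at least 5 points to a total of at least 15 leads to a phone interview by a trained research assistant if "this increase is still present or even more pronounced 2 weeks later".

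The forms are remote: "All self-report assessments will be conducted through the Qualtrics website", by a link emailed to the participant. At week 10, "we will also use the SCID-5 [31] to screen for other deteriorations in all participants".

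The arms differ in their other personal contact. GAF-ID participants are phoned by a lay counselor "weekly during the first 4 weeks and at weeks 6 and 8", and the counselors' training includes "how to monitor suicidality or other serious deteriorations during the intervention". For the control arm: "Participants in the PE group will receive neither assistance from lay counselors nor from clinical psychologists".

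The section on clinical psychologists adds that they receive a "standardized procedure on when and how they should do suicide risk assessment and handle serious participant deteriorations". The content of that procedure is not given.

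**The concern.** A rule that waits for confirmation works while forms keep arriving. Once a participant stops responding, neither condition can be met, and the section states no action for that case. A participant who scored positive and then went silent is handled like one who scored positive and then recovered: nobody calls.

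This is foreseeable. The forms are online self-reports, and the power calculation itself allows for 20 % attrition. The gap also falls unevenly. In GAF-ID, counselor calls continue whether or not a PHQ-9 is returned, and people who do not log in are reminded and then phoned. No comparable step is described for PE. What is at stake is participant safety: the trial would hold a recorded signal of suicidal thoughts or marked worsening with no stated response for several weeks.

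**Working it through.** The plan gives no figure for this point, so the check applies the stated rules to the stated schedule.

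**Inputs**
- PHQ-9 at baseline and weeks 2, 4, 6, 8 and 10 (Table 1, Outcome assessments).
- Both triggers need two positive forms, the second at the next 2-weekly occasion (Suicidality and serious deterioration).
- Next scheduled personal contact for a PE participant: the SCID-5 interview at week 10 (same section).

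**Case 1: first positive at week k, nothing returned afterwards (PE)**

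The participant has one of the two positives required, so neither trigger fires.
- Wait from signal to next scheduled contact = 10 − k.
- A responder whose signal persists is due a call at k + 2.
- Extra delay = 10 − (k + 2) = 8 − k.

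| First positive (week) | Wait to week 10 (weeks) | Call for persistent responder (week) | Extra delay (weeks) |
|---|---|---|---|
| 2 | 10 − 2 = 8 | 4 | 6 |
| 4 | 10 − 4 = 6 | 6 | 4 |
| 6 | 10 − 6 = 4 | 8 | 2 |
| 8 | 10 − 8 = 2 | 10 | 0 |

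The point therefore concerns first positives at weeks 2, 4 and 6. At week 8 a persistent responder would not be called before week 10 either.

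The delays are upper limits. They apply to signals that would have persisted. A responder whose next form was negative would get no call under the two-score rule, so for a non-returner in that position nothing has been delayed.

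**Case 2: only the next form is missed, all later forms positive (suicide item)**

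A later pair can still fire the trigger. The text does not say whether a missed form breaks a consecutive pair, so both readings are shown.

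| First positive (week) | Call if the gap does not break the pair | Call if it does | Persistent responder | Extra delay (weeks) |
|---|---|---|---|---|
| 2 | week 6 | week 8 | week 4 | 2 or 4 |
| 4 | week 8 | week 10 | week 6 | 2 or 4 |
| 6 | week 10 (form) | week 10 (interview) | week 8 | 2 |

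This is the milder case.

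**Baseline.** If baseline counts as an occasion, suicide-item positives at baseline and week 2 already make a pair, and the call is due at week 2. Case 1 is therefore about signals that are new after baseline.

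**How many.** The document gives neither the rate of positive forms nor the chance that a form is missed after one. The attrition allowance has no stated time point. Any head count would rest on an assumed share, so none is offered.

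**The case against.** The strongest reply is that this is operational detail which a condensed article leaves elsewhere, and that the article points to where it lies. The psychologists' procedure covers when to act as well as how, names serious deterioration as well as suicide risk, and is not limited to one arm. It may already deal with a missing form. That stands as a limit on the claim. It does not remove it: the article sets out thresholds, interval, callers and follow-on interviews, and the rule so stated gives a poor result when a form is missing. The procedure is also given to psychologists, whereas the first deterioration call belongs to a research assistant, so its reach there is less certain.

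Other mitigating points also stand. Acute suicidality is excluded at entry and referred. The entry SCID-5 is itself a phone contact. An incentive for staying to the last follow-up, the same in both arms, works against dropout.

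A reader might infer more than the text supports:
- *That PE participants have no safety follow-up.* Both triggers, and the referral route, apply to both arms.
- *That the two-score rule is wrong.* For people who respond it is a clinical choice, and nothing here challenges it.
- *That nobody is interviewed after week 10.* Table 1 lists no SCID-5 after week 10, but the main hypotheses expect SCID-5 results at the follow-ups, so the document is inconsistent here. The PHQ-9 is also scheduled at 3 and 6 months.
- *That GAF-ID is equally exposed.* Its counselor calls give a separate route by which a problem can surface.

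**Conclusion.** The point holds in a narrow form. Under the rules as written, a participant, mainly in PE, whose signal first appears at week 2, 4 or 6 and who then returns no forms triggers no stated contact before the week-10 interview. Compared with a responder whose signal persists, contact comes up to 6, 4 or 2 weeks later; from week 8 there is no extra delay.

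This rests on three conditions: the signal is new after baseline, it would have persisted, and the undisclosed procedure does not already cover a missing form. How often all three occur cannot be derived from the document. The issue is participant safety, not the validity of the primary comparison. It merits a change because the consequence for one person could be serious and the remedy is small.

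**What to change.** Add to the section on suicidality and serious deterioration, for both arms: a PHQ-9 not returned after a suicide-item score of at least 2, or after a rise of at least 5 points to at least 15, counts as not cleared. A reminder is sent. If the form is still missing after a period set in advance by the clinical team, shorter than 2 weeks, the person already assigned to that trigger phones the participant: the clinical psychologist for the suicide item, the trained research assistant for deterioration. The two-score rule for responders stays as it is. If the psychologists' procedure already provides this, a cross-reference to it in that section is enough.

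The cost is one sentence and a flag in the survey system for a missing form after a positive one. Participants are already interviewed by phone at entry, so the route exists. The downside is a few extra reminders and calls, some to people who merely forgot the form and some that go unanswered.

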## Discussion

To our knowledge, this will be the first study in Indonesia that investigates the effectiveness of an Internet-based psychological intervention for depression in a RCT. This trial offers new avenues for mental health treatments in LMICs, using Internet and additional support via an online voice call or phone call by lay counselors. If this intervention is effective, this treatment strategy can widen access for mental health services to many people from different locations in Indonesia.

Furthermore, it has been reported that the effect of an Internet-based cognitive-behavioral intervention for depression is still effective until 12 months after the intervention termination [45]. In this study, with assessments at post intervention (10 weeks from baseline) and follow-ups (3 months and 6 months from baseline), we will be able to assess the impact of this Internet-based behavioral activation intervention on depression in the longer term, including the impact on secondary outcomes. This study might be a starting point for showing the potential of using Internet-based intervention, and Internet-based BA in particular, to reduce the gap in mental health services availability in LMICs.

We also will try to identify factors that might contribute to depression and its recovery by collecting data regarding common comorbidity and other factors related to depression. It will provide information about the factors that require more attention in tailoring the Internet-based therapy program and implementing such an indicated intervention for depression in Indonesia.

### Trial status

Recruitment of the participants starts in September 2016. All participants are expected to finish their 6-month follow-up assessment by the end of 2017.

## Abbreviations

BA: Behavioral activation
BADS-SF: Behavioral activation for depression scale short form
FQ: Fear questionnaire
GAF-ID: Guided Act and Feel Indonesia
HIC: High-income country
IDS-SR: Inventory of depressive symptomatology Self-Report
LMIC: Low-middle income country
MEIM: Multigroup ethnic identity Measure
MSPSS: Multidimensional Scale of Perceived Social Support
PANAS: Positive and Negative Affect Scale
PE: Psychoeducation
PHQ-9: Patient Health Questionnaire-9
RCT: Randomized controlled trial
SCID-5: Structured Clinical Interview for DSM-5
VAS: Visual analogue scale
WHOQOL-BREF: The brief version of the WHO Quality of Life
